## Abstract

**Background:**

The coronavirus disease 2019 (COVID-19) is caused by severe acute respiratory syndrome coronavirus (SARS-CoV-2) and became pandemic after emerging in Wuhan, China, in December 2019. Several studies have been conducted to understand the key features of COVID-19 and its public health impact. However, the prognostic factors of COVID-19 are not well studied in the African setting. In this study, we aim to determine the epidemiological and clinical features of COVID-19 cases, immunological and virological courses, interaction with nutritional status, and response to treatment for COVID-19 patients in Ethiopia.

**Methods:**

A multi-center cohort study design will be performed. Patients with confirmed COVID-19 infection admitted to selected treatment centers will be enrolled irrespective of their symptoms and followed-up for 12 months. Baseline epidemiological, clinical, laboratory and imaging data will be collected from treatment records, interviews, physical measurements, and biological samples. Follow-up data collection involves treatment and prognostic outcomes to be measured using different biomarkers and clinical parameters. Data collection will be done electronically using the Open Data Kit (ODK) software package and then exported to STATA/SPSS for analysis. Both descriptive and multivariable analyses will be performed to assess the independent determinants of the treatment outcome and prognosis to generate relevant information for informed prevention and case management. The primary outcomes of this study are death/survival and viral shedding. Secondary outcomes include epidemiological characteristics, clinical features, genetic frequency shifts (genotypic variations), and nutritional status.

**Discussion:**

This is the first large prospective cohort study of patients in hospitals with COVID-19 in Ethiopia. The results will enable us to better understand the epidemiology of SARS-CoV-2 in Africa. This study will also provide useful information for effective public health measures and future pandemic preparedness and in response to outbreaks. It will also support policymakers in managing the epidemic based on scientific evidence.

*Trial Registration:* The Protocol prospectively registered in ClinicalTrials.gov (NCT04584424) on 30 October, 2020.

## Background

On March 11, 2020, the World Health Organization (WHO) declared Corona Virus Disease (COVID-19) to be a pandemic [1]. The current new emerging virus is a different strain of virus from SARS and MERS CORONA viruses. The difference is not only limited to genetic makeup but also in the clinical presentations, case fatality, and the rate of spread across the globe (surveillances). The swift spread of the virus is largely attributed to its stealth transmission, for which infected patients may be asymptomatic or exhibit only flu-like symptoms in the early stage. These undetected transmissions present a remarkable challenge for the containment of the virus and pose an appalling threat to public health [2]. COVID-19 has become one of the leading causes of mortality around the world.

As of August 03, 2021, there have been 200,508,148 confirmed cases and 4.26 million deaths reported worldwide and nationally 281,300 confirmed cases and 4,395 deaths reported [3]. To this end, the COVID-19 Global Research and Innovation Forum recommended each country and region to conduct research and generate evidence in their respective local context to strike the right balance between stopping transmission now and prepare for the future [4].

COVID-19 has also sparked fears of an impending economic crisis and recession [5]. Social distancing, self-isolation and quarantine, travel restrictions and border shut downs have led to a reduced workforce across all economic sectors and caused many jobs to be lost. Schools have been closed down, and the need for commodities and manufactured products has decreased [6]. Along with its high infectivity and fatality rates, there has been mass fear of COVID-19, termed as “coronaphobia”, that has generated a plethora of psychiatric manifestations across the different strata of the society [7]. The COVID-19 itself, multiplied by forced quarantine to combat the disease applied by nationwide lockdowns can produce acute panic, anxiety, obsessive behaviors, hoarding, paranoia, depression, and post-traumatic stress disorder (PTSD) [7, 8].

Several socio-demographic, clinical, immunological and nutritional factors are associated with COVID-19 disease progression. Evidence shows that COVID-19 disease progression is worse in people with suppressed immunity due to old age, pre-existing health conditions [9], and genetic conditions [10]. However, a comprehensive understanding of the underlying immunological process, particularly within cellular immunity, is still not well defined. The clinical disease spectrum of the SARS COV-2 ranges from subclinical or manifesting as unremarkable respiratory symptoms to severe respiratory complications such as pneumonia and respiratory distress.

There is growing literature highlighting obesity as a significant risk factor for the development of severe COVID-19. Body mass index (BMI) is an anthropometric measure used to assess obesity risk and has been observed as a risk factor in MERS-CoV [11] and influenza [12]. A recent systematic review showed that high BMI plays a significant role in COVID-19 severity in all ages, especially in the elderly population [13]. Obesity is associated with increased severity and mortality in pandemic H1N1 influenza and other respiratory viruses [14].

With the currently available evidence so far, children contribute 1–5% of total COVID-19 cases worldwide [15]. Asymptomatic disease in SARS-CoV-2 positive children ranged from 13% in China to 21% in Italy. Clinical features in symptomatic children are generally milder than adults; a very small proportion of those aged under 19 years have developed severe (2.5%) or critical disease (0.2%) [16].The USA and Chinese data showed bimodal age distribution among critically ill children, infants and adolescents > 15 years were more likely to be hospitalized due to COVID-19, and death was extremely rare with only a few numbers of reported cases [17].

Evidence on the effect of COVID-19 on pregnancy and its outcomes seems to be controversial. In some studies, pregnant mothers with confirmed COVID-19 infection were discharged without any major complications after giving birth. However, severe maternal morbidity resulting from COVID-19 and perinatal deaths has been documented in other studies [18]. There is also limited evidence about in utero infection and early positive neonatal testing. For example, a prospective cohort study conducted among pregnant women admitted to the hospital with confirmed SARS-CoV-2 infection in the UK revealed that 12 (5%) of 265 infants tested positive for SARS-CoV-2 RNA, six of them within the first 12 h after birth [19]. Contrary to this, infection has not been found in neonates delivered from pregnant women with COVID-19 based on a report from Hubei Province, China [20]. Further research, therefore, is required to determine the effect of COVID-19 on pregnancy and birth outcomes in our situation.

Nutrition is a key determinant of health [21]. More importantly, it is part of the treatment regimen for acute and chronic diseases and applies particularly to ailments for which an etiologic treatment has not yet been discovered and validated. An adequate diet is necessary to provide energy for the body’s functions and nutrients to build and repair tissues, prevent sickness, and help the body heal from illness [22]. A balanced diet also has a vital role in bolstering the immune response of an infected person against RNA viral infections [23]. There is sufficient evidence to demonstrate that the immune response can be weakened by inadequate nutrition [22, 23, 25]. The role of some nutrients in immune function and infectious diseases is well established, such as vitamin D [25].

In recent studies, COVID-19 is shown to be commonly complicated with coagulopathy, and the management of thromboembolism has significant importance in reducing mortality and morbidity [26, 27]. This indicates that a severe cytokine storm induces SARS-Cov-2 to lead to the coagulation cascade, causing thromboembolism, which is linked to abnormal parameters such as increases in fibrin, fibrin degradation products, fibrinogen, and D-dimer. Furthermore, immobility, systemic inflammation, platelet activation, endothelial dysfunction, and stasis of blood flow have been reported as the predisposing factors of thromboembolism [27]. The WHO recommended the use of low molecular weight heparin (e.g., enoxaparin), according to local and international standards, to prevent venous thromboembolism, when not contraindicated in COVID-19 patients [28]. However, the incidence of venous thromboembolism in COVID-19 patients hospitalized and under thromboprophylaxis is unclear.

To understand the negative impacts of COVID-19 on public health and key features pertinent to the disease, various studies are under investigation at the global level and they are contributing to delineating the characteristics of the disease and its lethality. Currently, it is recognized that a ‘one size fits all’ approach towards the design and implementation of interventions may not be appropriate. Therefore, global priorities, protocols, and intervention assessments have to be contextualized and adjusted to local needs and realities, including the translation of results. Therefore, this study aimed to determine the natural history of the disease; clinical features and management, epidemiological characteristics, immunological, virological courses and treatment response of the disease; effects of diets on the nutritional status on disease progression; effect of the disease on pregnancy and birth outcomes; and, the effect of traditional/modern treatment on COVID-19 outcome among patients admitted to treatment centers in Ethiopia.

## Methods/design

### Aim and study setting

In this multi-site cohort study, we aimed to determine the natural history of the disease; clinical features and management, epidemiological characteristics, immunological, virological courses and treatment response of the disease, effects of diets on the nutritional status on the disease progression, effect of the disease on pregnancy and birth outcomes, and the effect of traditional/modern treatment on COVID-19 outcomes among patients admitted to treatment centers in Ethiopia. Therefore, the study findings will generate scientific data for a systematic understanding of natural history, epidemiological characteristics, clinical features, and management of COVID-19 which will, in turn, enable the country’s health sector to develop strategies to prevent and control the pandemic before it poses further health and socioeconomic crises. The research question of this study is “Do different individual host factors and environmental situations influence clinical, epidemiological, and viral outcomes of COVID-19 infection?”.

The study will be conducted in all Federal treatment centers, including Ekakotebe, Yekatit-12, St. Peter Specialized hospitals, SPHMMC, Millennium hall center in Addis Ababa, and Regional Hospitals including Mekelle, Semera, Bahir Dar, Adama/Mojo, Hawassa, Jijiga, Harar, DireDawa, Metekel or Benishangul Gumuz, and Gambela dedicated to COVID 19 treatment.

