### Primary outcome and secondary outcomes

The primary outcome variables are treatment outcome (active cases, recovered, death or transferred for further treatment), recovery time, and duration of viral shedding (the time from the first positive RT-PCR results to the occurrence of the last positive RT-PCR results or negative RT-PCR results). The secondary outcomes include clinical symptoms and signs (major); co-morbidities; status at last follow-up (survival, severity, virus detection); laboratory biomarkers; duration of symptomatic phase, inpatient stay, ICU stay; viral loads; anti-SARS-CoV-2 antibody titer; imaging with results; therapeutic measures; plasma 25-hydroxyvitamin D concentrations; dietary history; micronutrient status (zinc and vitamin A); fasting blood sugar; weight, height, BMI; total cholesterol (TC), triglycerides (TG), HDL-C, LDL-C and body composition(waist circumference); genetic frequency shifts (genotypic variations); obstetric and gynecologic history; pregnancy status/test; clinical status; supplemental oxygen; non-invasive ventilation or oxygen delivery devices/ respiratory support. We will also collect confounding variables include socio-demographic variables (age, sex, education status); status cases at the time of enrollment; and months after the first positive test.

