### Data processing and statistical analysis

Data collection will be done electronically using the ODK software package and then exported to STATA/SPSS for data cleaning, management, and statistical analysis. The data will be cleaned and checked for outliers, all assumptions, and analyzed using appropriate statistical software (STATA, Python, and/or R statistic software).The analysis will be performed by trained personnel (epidemiologists, statisticians, health economists) using the appropriate statistical methods. Statistical analyses strategy will be based on specific study objectives and the nature of the outcome variables, the various assumptions to be assessed and associated scenarios to be considered, and the criteria to be used for decision-making at each stage including management of incomplete data, model building procedures, and evaluating the validity of models and the robustness of results. Data will be assessed for consistency, missing values, presence of outliers and implausible values, and different statistical assumptions including univariate and multivariate normality of distributions, the linearity of hypothesized relationships, the proportionality of hazard, and the presence of rare events among others.

A descriptive summary of the continuous variables will be reported as mean (± SD) and median (IQR), and categorical variables will be summarized as counts and percentages. A correlation or chi-square test will be performed for appropriate variables.

Predictors that have been identified as risk factors in the bivariate analysis will be entered into multivariable analysis to isolate independent determinants of the outcome. Multiple linear and generalized linear regression models will be fitted depending on the type of outcome variable. Cox-proportional hazard ratio (HR) will be used for time-to-event variables including the time to recovery, and other time to event variables. Time to event analysis, semi and parametric survival analysis will be conducted as appropriate.

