To take into account the multi-center cohort design, i.e., clustering of data by treatment centers and repeated measurements per subject over time, a multilevel modeling approach will be employed using mixed-effects modeling or generalized estimating equation. Incomplete data (missing values and lost-to-follow-up cases) will be handled using model-based approaches, such as full information maximum likelihood estimation and multiple imputation modeling after the missing data mechanisms and assumptions are evaluated. Regression models will be evaluated for potential problems including collinearity among predictors, omitted variables bias, and model over-adjustment (endogeneity). The final fitted models will be assessed for validity and robustness of results on a subsample of data not used in the model-building procedure. For this purpose, a random subsample from the original data will be kept before starting the analysis. Statistical significance will be considered at α < 0.05. However, to control for the inflated probability of Type-I error due to multiple hypotheses testing, P-values will be adjusted for false discovery rate using the Benjamini–Hochberg method. The results will be described as percentages, tables, figures, and association significance.

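### The rule for entering predictors does not separate mediators from confounders, so it can understate the diet effect that the nutrition aim asks about

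*Protocol article*

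**What the plan says.** The aim appears in Aim and study setting, and in almost the same words at the end of Background: "effects of diets on the nutritional status on the disease progression". The abstract's Background words the nutrition topic differently, as "immunological and virological courses, interaction with nutritional status, and response to treatment for COVID-19 patients in Ethiopia". The abstract's Methods ends its list of secondary outcomes with "genetic frequency shifts (genotypic variations), and nutritional status".

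Primary outcome and secondary outcomes lists "dietary history; micronutrient status (zinc and vitamin A); fasting blood sugar; weight, height, BMI", together with plasma vitamin D, among the secondary outcomes. The confounders it names are "socio-demographic variables (age, sex, education status); status cases at the time of enrollment; and months after the first positive test". Neither diet nor nutritional status is on that second list.

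Data processing and statistical analysis gives one concrete rule for building models: "Predictors that have been identified as risk factors in the bivariate analysis will be entered into multivariable analysis to isolate independent determinants of the outcome". The same section says in general terms that the strategy will follow the objectives. It later says that regression models will be evaluated for problems including "collinearity among predictors, omitted variables bias, and model over-adjustment (endogeneity", and does not say what would count as over-adjustment or what would then be done.

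**The concern.** If diet influences progression through nutritional status, then nutritional status is a mediator. Diet and the mediator will both tend to be associated with the outcome, so both will tend to pass a bivariate screen. A model holding both gives a diet coefficient from which the mediated part has been removed. That coefficient answers whether diet matters beyond nutritional status, which is close to the complement of the stated aim.

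A diet effect that works mainly through nutrition could then be reported as weak, or as not an independent determinant. Complete data would not correct this, because the cause is the choice of covariates.

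**Working it through.** The plan states no figure on this point, so there is none to reproduce. The check has two parts.

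**Reading the text.** The aim places nutritional status between diet and progression. The entry rule selects on association alone, and a mediator passes such a screen as readily as a confounder. Nothing stated after the rule requires a mediator to be taken out again.

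**Mechanism.** Let D be diet and M a nutritional marker, with M = a·D + error and logit(p) = constant + b·M + c·D. A model with D and M estimates c. A model with D alone estimates approximately c + a·b. The joint model therefore drops a·b, and the mediated share is a·b / (c + a·b).

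**Inputs from the article** (Sample size and sampling procedures): 6,390 patients, 20% loss, design effect 2.5, 28% deaths. Effective size: 6,390 × 0.8 / 2.5 = 2,044.8, taken as 2,044.

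**Assumptions, not in the article:** diet as a two-level variable split evenly, M with unit error variance, the values of a, b and c below, no confounding, each test at 0.05 without false-discovery adjustment, 500 simulated data sets per row. The simulated death rate was 28.4% to 28.6%.

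| a, b, c | Mediated share a·b/(c + a·b) | Diet alone: OR (significant) | Diet + marker: OR (significant) | Diet non-significant in the joint model when both pass the screen |
|---|---|---|---|---|
| 0.5, −0.6, 0 | 0.30/0.30 = 100% | 0.75 (81%) | 1.00 (5%) | 97% |
| 0.5, −0.6, −0.15 | 0.30/0.45 = 67% | 0.65 (99%) | 0.85 (33%) | 67% |
| 0.5, −0.6, −0.30 | 0.30/0.60 = 50% | 0.57 (100%) | 0.74 (82%) | 18% |
| 0.25, −0.6, −0.15 | 0.15/0.30 = 50% | 0.76 (79%) | 0.86 (34%) | 57% |

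The closed form agrees in the first row: exp(0.5 × −0.6) = exp(−0.30) = 0.74, against a simulated 0.75.

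**A second simulation** used continuous diet and full mediation, with a diet–marker correlation of 0.3 or 0.5, b of 0.3 or 0.5, event rates of about 10% to 28% and 600 runs per setting. The total odds ratio per SD runs from exp(0.3 × 0.3) = 1.09 to exp(0.5 × 0.5) = 1.28. With 2,045 patients, diet alone was significant in 23% to 100% of runs. The joint model gave 1.00 and was significant in 4% to 6%. With 6,390 × 0.8 = 5,112 patients and no design effect, the figures were 47% to 100% against 3% to 6%.

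**The case against.** The strongest reply is that the article never says diet and nutritional status share a model. The rule is conditional and names no variable, and the outcomes section lists both among secondary outcomes. A reader might infer that the plan does put them together; the text supports only that the rule would do so if both pass the screen. This stands, and the point is worded accordingly.

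The aim is also garbled. It could be a slip for diet and nutritional status as two separate exposures, and a joint model is then a reasonable choice. The chain is the likeliest reading, not the only one.

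The plan also ties its strategy to the objectives and lists over-adjustment, which is this very problem. That is a real safeguard in intent. But with no criterion or action it does not settle which model is reported, and the bivariate screen remains the only concrete selection rule.

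The bivariate step would itself show a crude diet association, so the effect would not be invisible. That also stands. What is missing is a total effect of diet adjusted for confounders.

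A reader might take the differing roles of nutritional status (interaction, outcome, intermediate) as a contradiction. It is not one: a variable can be an outcome of diet and an exposure for progression.

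Finally, a full protocol or analysis plan, not shown, may set covariates for each objective. The point therefore concerns only the rule that the article states.

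**Conclusion.** The point holds in a conditional form. On the most natural reading of the aim, the stated entry rule does not fit it. When diet and a nutritional marker both pass the screen, the joint model understates the diet effect.

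The size cannot be derived from the article. Under the assumed effects it runs from moderate attenuation at half mediation (0.57 to 0.74, or 0.76 to 0.86) to complete loss at full mediation (0.75 to 1.00). A reader might infer that a real diet effect would be reported as none. That follows only if the whole effect is mediated; at half mediation, diet stayed significant in 82% or 34% of runs, depending on the strength of the effects.

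The conclusion rests on the chain reading of the aim, on both variables passing the screen, and on the over-adjustment check having no rule attached.

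**What to change.** For the nutrition aim, exempt diet and nutritional status from the bivariate screen and prespecify two models:

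1. The total effect of baseline diet on progression, adjusted for pre-illness confounders (age, sex, education, pre-existing conditions), without BMI, vitamin D, zinc or vitamin A.
2. The effect of baseline nutritional status on progression, adjusted for diet and the same confounders.

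Model 1 gives the total effect and does not isolate the part acting through nutritional status. If that part is the target, add a prespecified mediation analysis. The aim should be reworded so that it is clear which is meant. If an interaction with nutritional status stays among the aims, it needs its own prespecified product term.

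The cost is analysis wording and one extra model, with no new patients. Diet, weight, height and vitamin D are on the baseline list. Zinc and vitamin A appear only among the outcomes, so confirm that a baseline value exists before using them in model 2. The downside is a few more tests in the Benjamini–Hochberg family.

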### Study design and period

A multi-center prospective open cohort study design on COVID-19 confirmed cases in Ethiopia conducted from December 01, 2020 to December 2021. Like many other disease-specific general open cohorts, such as in Framingham Heart Study and the Ethiopia Netherlands AIDS Research Project (ENARP) studies, the study intends primarily to measure the incidence of several epidemiological, clinical, virological, and immunological outcomes of COVID-19 cases [29, 30]. The cohort will be an unbiased extensive routine collection of clinical, radiographic, laboratory, and clinical management, virological, immunological and nutritional data, which helps to detect and address emerging research priorities without relying on a priori hypothesis.

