### Study population

This study will enroll individuals with confirmed infection with COVID-19 at selected Federal and Regional Hospitals irrespective of their differences (age, sex, symptoms, severity, and any other conditions). The patients' follow-up will be done strictly within the management adapted to their infection.

Individuals/patients in the study hospital or area will be eligible for inclusion if they meet the following criteria: (1) patient is admitted to selected treatment centers (Federal and Regional’s Hospitals) with COVID-19 confirmed by RT-PCR; and (2) consents to be enrolled in the follow-up study and provide all necessary information/data, blood sample, and nasopharyngeal swab for testing. Patients will be excluded if: (1) a subject deprived of freedom, subject under a legal protective measure; (2) refusal by a participant, parent or appropriate guardian or representative; (3) not willing to stay 12 months in the cohort in Ethiopia; (4) is already involved in the COVID-19 clinical trial or other interventional studies; (5) not capable of understanding or complying with the study protocol or provide consent; (6) anticipated transfer to another hospital that is not a study site within 72 h.

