### Sample size and sampling procedures

The estimated sample size for this study is 6,390, based on the assumptions of a 28 percent death rate from a retrospective study, a design effect of 2.5, and a 20 percent loss to follow-up. A baseline evaluation or assessment will be performed immediately after screening. After baseline assessment, all patients will be followed-up daily until discharge according to WHO and National discharging guideline and followed as per schedule after discharged. Study subjects enrolled will be followed up for 12 months after enrollment for the specific objective related to virology and immunology, clinical course of the disease, response to treatment, effect of COVID-19 in pregnant mothers and birth-related effects of COVID-19. Enrolled cases will be followed up at 2 weeks, 3 months, 6 months, 9 months, and 12 months post-discharge. A visit window of ± 7 days may be applied to these visits. Patients discharged after recovery will be followed up according to the follow-up schedule.

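### With only infected participants and no reference group, the cohort cannot estimate the effect of COVID-19 on pregnancy and birth outcomes; the aim should be restated as descriptive and its birth outcomes named

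*Protocol article*

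**What the plan says.** The Background section argues for this objective: "Further research, therefore, is required to determine the effect of COVID-19 on pregnancy and birth outcomes in our situation". Its closing paragraph and the section Aim and study setting both include, among what the study will determine, the "effect of the disease on pregnancy and birth outcomes". The section Sample size and sampling procedures assigns 12 months of follow-up to several objectives, one of them the "effect of COVID-19 in pregnant mothers and birth-related effects of COVID-19".

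The design is described as "A multi-center prospective open cohort study design on COVID-19 confirmed cases in Ethiopia" (Study design and period). The first inclusion criterion is that the "patient is admitted to selected treatment centers (Federal and Regional’s Hospitals) with COVID-19 confirmed by RT-PCR" (Study population).

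On this topic, the section Primary outcome and secondary outcomes lists "obstetric and gynecologic history; pregnancy status/test". The sections Baseline assessment and Follow-up visits add a urine pregnancy test in women.

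**The concern.** An effect of a disease is a contrast between people who have it and comparable people who do not. The stated aim asks for that contrast, but eligibility removes one side of it. A proportion of women with an adverse pregnancy or birth outcome in this cohort would combine the background risk in the population with whatever infection adds, and the design gives no means of separating the two. If the aim stays as worded, such a proportion could be read as the answer to it.

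An objective on birth outcomes also needs birth outcomes. The outcome section goes down to individual lipid fractions and waist circumference, yet names nothing about delivery or the newborn. At stake is what the study may conclude on one of its stated aims.

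**Working it through.** The document gives no figure for this objective, so there is none to reproduce. The check compares the aim with the design and then with the data items.

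**Is there a contrast?**

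- Quantity implied by the aim: effect = risk of the outcome in infected pregnant women − risk in uninfected pregnant women (or the ratio of the two).
- First term: estimable in principle, from women pregnant at enrolment.
- Second term: needs uninfected women or an outside reference. RT-PCR confirmation is required of everyone, so the number of uninfected participants is 6,390 × 0 = 0. After the assumed 20% loss, 6,390 × 0.80 = 5,112 participants remain, and the uninfected number is still 0. The result is the same for any other total.
- Outside reference: none is named in the sections on aim, design, population, sample size, outcomes or analysis.
- Rescue by analysis: the section Data processing and statistical analysis plans multivariable regression, Cox models, multilevel models or generalised estimating equations, and multiple imputation. These adjust or complete comparisons among people who were observed. None can supply an exposure level that no participant has.

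**Is there an endpoint?**

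| Place in the article | Items on pregnancy or birth |
|---|---|
| Primary outcomes | None specific (treatment outcome, recovery time, viral shedding) |
| Secondary outcomes | Obstetric and gynaecological history; pregnancy status or test |
| Baseline assessment | Urine pregnancy test |
| Follow-up visits | Urine pregnancy test |
| Named confounders | No gestational age |

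No row holds delivery date, gestational age at birth, birth weight, pregnancy loss, stillbirth, neonatal infection or neonatal death.

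**What the cohort can deliver.** Maternal survival, severity, ICU stay and oxygen support are on the secondary list and apply to pregnant women as to others. Severity and status at enrolment are recorded, so comparisons among infected women by severity are possible. The same comparison by gestational age at infection needs one more variable. Twelve months of follow-up is long enough to reach delivery for women pregnant at enrolment.

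**The case against.** The strongest reply is that the word effect is used loosely. The Background cites a prospective cohort of infected pregnant women in which 12 of 265 infants tested positive, and it points to in utero infection and early neonatal positivity as gaps; neither question needs uninfected women. The section Study design and period says the study mainly measures incidence among cases without prior hypotheses, and the research question concerns host and environmental factors. This has force, but it supports rewording the aim. The text still says effect of the disease in three places, and the Background calls the evidence on that effect controversial, which rates among infected women alone cannot settle.

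The second reply concerns endpoints, and more of it stands. The secondary list is introduced as non-exhaustive, the questionnaire and case report form are not shown, an article condenses its full protocol, and follow-up is expressly meant to serve birth-related objectives. A reader might infer that no birth outcome will be collected. The document does not support that; it shows only that none is named. Nor are the pregnancy items mere baseline descriptors, since the pregnancy test is repeated at follow-up.

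A reader might also infer that crude rates will be published as attributable effects, or that risk ratios will be distorted by women admitted for obstetric reasons. The document states neither, and it gives no pregnancy risk from which the size of a distortion could be worked out.

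Finally, this is one aim among several. It is absent from the Abstract's aims and outcomes and does not drive the sample size. That is correct and limits the weight of the point.

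**Conclusion.** The point holds in two parts of different strength.

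Firm: an effect of COVID-19 against no COVID-19 on pregnancy and birth outcomes is not identifiable from this cohort at any sample size, because infection status does not vary and no reference is named. This rests only on the stated eligibility and design. It would change only if the full protocol contained an uninfected comparison group or a reference rate that the article omits.

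Softer: the article names no delivery or newborn outcome for an aim that promises them. This assumes that the article's lists reflect the plan; the case report form could fill the gap.

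It would go too far to say that the whole pregnancy objective fails. A descriptive account, and comparisons among infected women, remain within reach. How precise they would be cannot be judged, because no expected number of pregnant participants is given. No numerical bias can be attached to the point, and the primary outcomes are untouched. The change should be made because it alters what the study may claim.

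**What to change.** 1. Reword the objective in the closing paragraph of the Background, in Aim and study setting, and in Sample size and sampling procedures. Suggested text: to describe pregnancy and birth outcomes among women with COVID-19, and to compare them within the cohort by severity at enrolment and gestational age at infection. State that no effect of COVID-19 against no COVID-19 will be claimed.
2. Add to the secondary outcomes, for women pregnant at enrolment, what can be obtained from maternal interview or care records at visits already scheduled: delivery date, gestational age at delivery, birth weight, live birth or stillbirth, neonatal death, and any neonatal SARS-CoV-2 result from routine care. Record gestational age at infection so that the second comparison can be made.
3. Add no new neonatal test. Newborns are not participants under the stated eligibility, so a test would be an extra procedure outside the present design.

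The cost is a narrower claim and a few more form fields, or none where the case report form already holds them. No new group, site or visit is needed.
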